## Abstract

**Background:**

Malnutrition is a complex and costly condition that is common among older adults in the United States (US), with up to half at risk for malnutrition. Malnutrition is associated with several non-medical (i.e., social) factors, including food insecurity. Being at risk for both malnutrition and food insecurity likely identifies a subset of older adults with complex care needs and a high burden of social vulnerability (e.g., difficulty accessing or preparing meals, lack of transportation, and social isolation). US emergency departments (EDs) are a unique and important setting for identifying older patients who may benefit from the provision of health-related social services. This paper describes the protocol development for the Building Resilience and InDependence for Geriatric Patients in the Emergency Department (BRIDGE) study. BRIDGE was designed to assess the feasibility of an ED-based screening process to systematically identify older patients who are at risk for malnutrition and food insecurity and link them to health-related social services to address unmet social needs and support their health and well-being.

**Methods:**

Phase 1 efforts will be formative and focused on identifying screening tools, establishing screening and referral workflows, and conducting initial feasibility testing with a cohort of older patients and ED staff. In phase 2, which includes process and outcome evaluation, the screening and referral process will be piloted in the ED. A partnership will be formed with an Area Agency on Aging (AAA) identified in phase 1, to assess resource needs and identify community-based social services for older ED patients who screen positive for both malnutrition risk and food insecurity. Data on screening, referrals, linkage to community-based social services, and patient-reported quality of life and healthcare utilization will be used to assess feasibility.

**Discussion:**

The tools and workflows developed and tested in this study, as well as learnings related to forming and maintaining cross-sector partnerships, may serve as a model for future efforts to utilize EDs as a setting for bridging the gap between healthcare and social services for vulnerable patients.

## Background

Malnutrition is common among older adults [1] and contributes to poor health and premature death [2–5]. The annual economic burden of disease-associated malnutrition in the United States (US) is over $155 billion, with more than $51 billion of that cost attributable to older adults [6, 7]. Malnutrition is a complex, multifaceted condition and is associated with numerous risk factors that are often synergistic or bidirectional in nature. Clinical risk factors include, but are not limited to, polypharmacy, chronic medical conditions, depression, poor oral health, impaired swallowing, and frailty. Non-medical (i.e., social) risk factors include, but are not limited to, lack of transportation, loneliness and social isolation, low-quality diets, and food insecurity [6, 8, 9].

Food insecurity (i.e., lack of access or inability to afford adequate food) is a critical modifiable social risk factor for malnutrition and is a common problem among older adults in the US [10]. Food-insecure older adults have high rates of medical problems such as diabetes, depression, and heart disease, and food insecurity likely contributes to worse health outcomes [11]. Older adults with complex medical needs often also have social needs that can contribute to increased risk for both malnutrition and food insecurity. Breaking the cycle of food insecurity leading to worse health outcomes resulting in worsening food insecurity is essential to optimize health outcomes for these patients. One approach to addressing social needs is through existing community-based social services, which can be leveraged to help prevent or reduce risk in community-dwelling older adults. For example, though it is underutilized [12], there is evidence that enrolling older adults in food assistance programs, such as the Supplemental Nutrition Assistance Program (SNAP), can improve health status and enable patients to remain in their homes [7, 13]. There is also evidence that home-delivered meal programs, which serve a largely homebound older adult population, can improve nutritional status while also reducing social isolation and falls [7, 14]. For particularly vulnerable populations, such as those transitioning from hospital to home, medically tailored home-delivered meals are associated with decreased healthcare utilization and reduced spending on medical care [15, 16].

Using a clinical setting, such as an emergency department (ED), to screen for malnutrition risk and food insecurity may be an effective “foot in the door” approach that has the potential to improve health outcomes and decrease healthcare utilization [7, 13, 17]. EDs in the US receive over 20 million visits by older adults annually and are a common and essential site of care for individuals with limited financial resources [18]. Recent estimates indicate that approximately 15% of older patients seeking ED care are malnourished, and almost half are either malnourished or at risk of malnutrition [1, 6]. Further, food insecurity was identified as an important contributing factor to malnutrition for more than 25% of ED patients with malnutrition [1, 6]. Thus, based on these estimates, a national ED-based screening intervention has the potential to impact over 500,000 affected older adults.

Despite the potential impact of screening for malnutrition and food insecurity, implementing a new process in an ED setting, where time is at a premium, may be challenging and require special considerations to avoid overburdening the already busy staff. In addition, while the existing staff is clinically trained, they may lack knowledge of social risk factors for malnutrition, including food insecurity, and, as such, may not understand the need to screen in the ED. ED staff may also be unaware of local community-based social services and lack a standardized process for connecting at-risk patients to necessary resources in the community. Though there is growing support for using existing community-based services to address social needs, coordination between clinical and community settings remains fragmented and often ineffective [19]. Cross-sector partnerships may help address social needs and are associated with improved healthcare utilization and spending [20].

This paper describes the protocol for the Building Resilience and InDependence for Geriatric Patients in the Emergency Department (BRIDGE) study, which aims to establish a simple, sustainable, and scalable ED-based process to systematically identify older patients who are at risk for malnutrition and food insecurity and link them to community-based social services to reduce risk and improve overall health and well-being.

## Methods

The screening and referral process will be developed and tested across 2 distinct phases (described in more detail below) at the University of North Carolina Hospitals Emergency Department (UNC ED), located in Chapel Hill, NC. The UNC ED provides 24-h emergency care for approximately 65,000 patients per year, including ~ 15,500 patients age 60 years and older, and serves a population that is diverse in ethnicity, socioeconomic status, and rural versus urban residence.

### Phase 1: Developing an ED-based screening and referral process

We will identify the existing screening tools, establish workflows, and conduct initial feasibility testing with UNC ED staff and patients. The primary aim is to learn how screening for malnutrition and food insecurity could best be incorporated into the existing workflow for the ED staff, including nurses, nursing assistants (NAs), and case managers (CMs). Throughout phase 1, we intend to use evidence-based strategies to guide the development and implementation [21, 22], such as the Consolidated Framework for Implementation Research (CFIR) [23] and the Plan-Do-Study-Act (PDSA) method [24], to help us quickly test, modify, and improve the screening tool and workflows. Phase 1 findings will be used to inform the ED-based screening and referral process, which will be piloted and evaluated in phase 2.

#### Identifying screeners for malnutrition and food insecurity

We will leverage existing screening tools for malnutrition and food insecurity, with consideration for the settings in which they were designed for and studied. For example, the two-item Malnutrition Screening Tool (MST) is a validated malnutrition risk screener and recommended for use among older adults in inpatient settings [25] and is already used in inpatient, acute care settings at UNC. The two-item Hunger Vital Sign (HVS) food insecurity screener is recommended for use in clinical settings [26] and recommended for use among older adults by AARP [27].

To select which screeners will be used for feasibility testing within the ED, multiple screeners will be combined into a questionnaire and tested with a small cohort of older, English-speaking patients who are 60 years of age and above and who seek care at the UNC ED. In addition to the malnutrition and food insecurity screener items, the questionnaire will assess for unmet social needs, including housing, social support, transportation, and financial strain. The questionnaire will also include items to gauge patient interest in and receptivity to receiving information about various community-based resources and assistance connecting with social services (e.g., SNAP, food pantry, congregate meal sites, home-delivered meals, transportation, and in-home meal preparation assistance). During this initial testing with patients, the questionnaire will be administered by research staff. Analyses will include descriptive statistics of patient demographics, screening questions, and additional items, such as acceptability and comprehension of screening questions, percentage of positive screens for malnutrition, food insecurity and both malnutrition and food insecurity, additional unmet social needs identified, and willingness of patients to receive assistance.

#### Engaging ED stakeholders and establishing workflows

Throughout phase 1, input will be solicited from UNC ED staff to understand their roles and associated workflows. Input will also include which ED staff roles may be best suited for this new workstream, their initial impression of the proposed screening and referral process, and any possible barriers or facilitators, including leadership buy-in. As we plan to incorporate the final screening tool and workflows into UNC’s electronic health record (EHR), Epic, we will solicit ED staff preferences related to where the screener is placed in Epic and explore the possibility of automated alerts.

Information may be collected using a variety of methods, including semi-structured informational interviews and soliciting feedback during staff meetings. Semi-structured interview guides will be developed using relevant domains and key constructs from CFIR [23], including those from the inner setting (e.g., implementation climate, compatibility, leadership engagement, tension for change) and characteristics of individuals (e.g., knowledge and beliefs about the intervention). Interviews will be conducted by the study staff, audio-recorded, and transcribed. A rapid analysis approach will be used to analyze the qualitative data [28, 29].

#### Feasibility testing with ED staff

Feasibility testing of the malnutrition and food insecurity screener and workflows will be conducted with a subgroup of older patients and appropriate UNC ED staff (e.g., NAs and CMs), potentially starting with a paper-based version of the screening tool. Rapid-cycle testing, such as PDSA [24], will be used to identify barriers and test solutions prior to full implementation. Throughout the testing, the workflows will be modified as necessary and the staff will serve as “champions” when the process is broadly implemented across the ED in phase 2.

#### Engaging community stakeholders and establishing partnerships

A critical component to the success of the study will be engaging with community stakeholders and establishing a cross-sector partnership with an Area Agency on Aging (AAA), a public or private agency appointed by the state to assist or coordinate services for older adults and persons with disabilities at the regional and local levels [30]. The AAA will accept direct referrals from the UNC ED for older patients who screen positive for malnutrition risk and/or food insecurity, follow up with patients to assess for additional resource needs, identify referral options, and provide or coordinate services.

In phase 1, we plan to identify and assess potential AAA partners and gain a better understanding of the geographic area (counties) served, availability of programs and services, service providers, program eligibility, needs assessment, capacity in the community to meet the social service needs of at-risk patients, and willingness and capabilities of the AAA to partner and share data.

During the process of establishing a partnership, we will track and document learnings, guided by CFIR [23]. This will likely include conducting semi-structured interviews to capture lessons learned and best practices about establishing a clinical-community partnership and data collection and reporting processes. In preparation for phase 2, we will work closely with the selected AAA to identify key data points, develop a plan for bidirectional data sharing, and create an efficient and reliable referral pathway.

### Phase 2: Testing the ED-based screening and referral process

In this phase, we plan to implement and evaluate the ED-based screening and referral process developed in phase 1. Older UNC ED patients who screen positive for both malnutrition risk and food insecurity will be referred to a local AAA to assess at-risk patients for additional related social needs and connect them to appropriate supports and services. Assuming approximately 10% of UNC ED older patients will screen positive (i.e., be at risk for both malnutrition and food insecurity), we plan to screen at least 2200 patients who enter the ED and enroll approximately 220 patients, using continuous screening and enrollment. Patients will not be randomized; all eligible patients will be screened, and a single-arm design will be used to evaluate the feasibility based on the proportion of patients screened and linked to services.

We will also conduct preliminary evaluations on the impact of the screening and referral process on malnutrition, general health, and other patient-reported outcomes. Details of the workflow will be determined during the formative work and testing in phase 1, though we will continue to assess the feasibility and sustainability in phase 2. Once workflows have been finalized, we will collaborate with the stakeholders at UNC’s ED and the selected AAA partner to develop protocols for each group involved (e.g., nursing, social work, and the AAA), which will serve as guides for the screening, referral, and documentation processes in phase 2.

A conceptual model of the screening and referral process is included in Fig. 1. Moving from left to right, the model shows the potential pathway (in solid arrows) for older patients who enter the ED and are screened for both malnutrition risk and food insecurity. If positive for both, the patient will be connected to a local AAA, which will follow up with the patient to assess resource needs and make referrals to community-based organizations that provide social supports and services. Funding will be available to support the care coordination work of the AAA and community-based organizations in providing services, particularly when programs have waitlists. We hypothesize that patients who are successfully connected with the needed services will have better outcomes at 3-month post, including decreased risk of malnutrition and food insecurity and decreased healthcare utilization. We anticipate that patient characteristics and clinical intervention from their primary care physician (PCP) may serve as mediators or moderators, which are depicted by dashed arrows.

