#### Data collection and analyses

Data will be collected from multiple sources and entered by research staff into REDCap, a secure, web-based database that meets or exceeds NIH security requirements, and stored and maintained by UNC. Process outcomes will include the proportion of eligible patients for whom malnutrition and food insecurity screens are completed, the proportion of screens that are positive, the number of referrals made from the UNC ED to the AAA, the number of patients contacted by the AAA, and the number and status of referrals made by the AAA to other social service programs and providers. Healthcare utilization outcomes will be selected based on data points available in Epic and, if possible, may include a retroactive review of utilization data from 6-month pre-enrollment, as well as up to 6-month post-enrollment. Patient-reported outcomes will be collected at the time of enrollment (baseline) and 3-month post-enrollment and will likely include single items of overall health and quality of life [31]. Malnutrition and food insecurity risk will also be re-assessed with a 3-month follow-up phone call. A formal data analysis plan will be developed during phase 1, and further analysis of the data will be explored as the study progresses.

In addition, we will continue to gather stakeholder perspectives throughout the implementation to determine if the intervention is feasible and sustainable, guided by CFIR [23]. Periodic reflections with the ED and AAA staff champions or key implementers will be used to understand implementation phenomena, including unplanned adaptations and real-time barriers or facilitators [32]. Qualitative data will be collected and analyzed in a similar approach as in phase 1.

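### Phase 2 re-screens patients who were selected for positive screens, without a comparator, so a lower positive rate at 3 months cannot be read as impact or benefit

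*Protocol article*

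**What the plan says.** All references are to the protocol article.

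- **Who enters phase 2.** Under Phase 2: Testing the ED-based screening and referral process: "Older UNC ED patients who screen positive for both malnutrition risk and food insecurity will be referred to a local AAA". The assumed joint positive rate is about 10%, and "we plan to screen at least 2200 patients who enter the ED and enroll approximately 220 patients".
- **Design.** Patients are not randomised, and "a single-arm design will be used to evaluate the feasibility based on the proportion of patients screened and linked to services".
- **Outcome re-measured.** Under Data collection and analyses: "Malnutrition and food insecurity risk will also be re-assessed with a 3-month follow-up phone call". That section describes no follow-up of screened patients outside the referral pathway and no second screen before services start. It defers a formal analysis plan to phase 1.
- **What is to be concluded.** The same Phase 2 section adds: "We will also conduct preliminary evaluations on the impact of the screening and referral process on malnutrition, general health, and other patient-reported outcomes". In its account of the conceptual model, it hypothesises that patients whose link to services succeeds will have "better outcomes at 3-month post, including decreased risk of malnutrition and food insecurity and decreased healthcare utilization". Limitations and challenges adds an aim to supply evidence on the benefits of paying for social services.
- **What is acknowledged.** Limitations and challenges covers ED workload, staff knowledge, service capacity and waitlists. It mentions neither selection on the outcome nor regression to the mean.

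**The concern.** Two of the phase 2 outcomes are the variables used to select the cohort. Every enrolled patient is positive on both screens at baseline, so nobody can move from negative to positive. False positive screens, transient illness around the ED visit, and ordinary disagreement between two administrations all show up as improvement. The second administration is also by telephone rather than in the ED, which may add disagreement.

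The design described therefore cannot separate a programme effect from the change expected without one. The text nevertheless speaks of impact, states a directional hypothesis, and aims at evidence of benefit. A fall from 100% could be reported as support for the programme whether or not it works.

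**Working it through.** **1. The plan's own figure.** 2200 screened × 0.10 = 220 enrolled, which agrees with the protocol. No alpha, power or effect size is stated, so there is no power figure to reproduce.

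**2. Baseline.** Under the Phase 2 referral rule, the positive rate among those enrolled is 220/220 = 100% on each screen and on both.

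**3. Expected rate at 3 months with no effect.** Let p be the positive rate among screened patients, assumed the same on both occasions, and let kappa be agreement between the two occasions. Then P(positive on both occasions) = p² + kappa × p(1 − p). Dividing by p gives

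P(positive at 3 months | positive at baseline) = p + kappa × (1 − p).

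The document gives p = 0.10 for joint positivity. For malnutrition risk alone, the Background puts almost half of older ED patients as malnourished or at risk, so p = 0.50 is used as a round figure. Kappa is not in the document and is assumed.

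| Assumed kappa | Still positive on both (p = 0.10) | No longer positive on both | Still positive, malnutrition risk (p = 0.50) | No longer positive |
|---|---|---|---|---|
| 0.8 | 0.10 + 0.72 = 82% | 18% (40 of 220) | 0.50 + 0.40 = 90% | 10% (22 of 220) |
| 0.6 | 0.10 + 0.54 = 64% | 36% (79 of 220) | 0.50 + 0.30 = 80% | 20% (44 of 220) |
| 0.4 | 0.10 + 0.36 = 46% | 54% (119 of 220) | 0.50 + 0.20 = 70% | 30% (66 of 220) |

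The malnutrition columns ignore the fact that enrolled patients are also food insecure. If the two risks are associated, persistence would differ somewhat. Recovery from acute illness that lowers the rate in everyone would add to the fall.

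**4. Incomplete follow-up.** The counts assume all 220 are reached. Consent for outcome data is sought only at the 3-month call (Eligibility criteria for ED patients). If 50% were reached (110, an assumption), the joint counts become about 20, 40 and 59. The percentages do not change if those reached are typical.

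**5. Second route to the same direction.** Hold true status fixed, take 10% true joint prevalence, and assume errors independent between occasions. With assumed sensitivity 0.8 and specificity 0.95:

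- screen positive = 0.10 × 0.8 + 0.90 × 0.05 = 0.125
- truly positive among them = 0.08 / 0.125 = 0.64
- positive again = 0.64 × 0.8 + 0.36 × 0.05 = 0.53, so 103 of 220 turn negative.

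Over sensitivity 0.7 to 0.9 and specificity 0.90 to 0.98, 36% to 75% stay positive, that is 140 down to 54 of 220 apparent improvements.

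**6. Why a test against baseline would be uninformative.** The protocol names no test; this only shows what one would do. With k patients turning negative and none able to go the other way, exact two-sided McNemar p = 2 × 0.5^k: 0.0625 at k = 5 and 0.031 at k = 6, which is 2.7% of 220. Even at kappa 0.95, 220 × 0.90 × 0.05 = 9.9 patients are expected to turn negative, and the chance of at least 6 is 0.93 with full follow-up (0.38 with 110 reached). Only perfect agreement with no natural change gives no fall.

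**The case against.** The strongest reply is that the faulty analysis is not in the document. No before-after test, significance level or success threshold is stated, the analysis plan is deferred, and a condensed article may leave that detail out. This stands: a reader might infer that a paired test is planned, and the text does not say so. It does not remove the point, because the article itself fixes the enrolment rule, the single arm, the re-screen and the wording of the hypothesis. A later plan cannot create a re-screen comparator outside the referred cohort from the data described.

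Other stronger readings are tempting and are not supported:

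- **Regression alone would confirm the hypothesis.** The hypothesis concerns patients successfully linked to services, so it may mean connected versus not connected within the cohort. Both groups share the regression, and that contrast is not forced to improve: with equal null rates, its simulated type I error was 0.050. It is, however, open to confounding by who can be reached and served, and the article does not state it.
- **All outcomes must improve.** Self-rated health, quality of life and utilization are not selection screens. They may regress after an index ED visit, but they can move either way. A numeric screener score can also worsen in individuals.
- **The change will size the larger studies.** The Discussion says only that the findings prepare for larger studies of effect.
- **The study fails its purpose.** The main aim is feasibility, and the impact work is labelled preliminary.

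One complication lies in the article itself. Engaging community stakeholders and establishing partnerships words AAA referral as covering either risk or both. The argument here rests on the Phase 2 section, which requires both.

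**Conclusion.** The point holds for the two screening outcomes. Yes/no screen status starts at 100% positive by selection, can only stay or fall, and would be expected to fall without any effect. That direction follows from the document, given anything short of perfect agreement over 3 months.

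The size is illustrative. With assumed kappa 0.8 to 0.4, 18% to 54% would no longer be jointly positive at the protocol's 10% rate, and about 10% to 30% would no longer be positive for malnutrition risk alone at a prevalence near 50%. These figures assume a stable rate in the screened population.

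The proportions screened, referred and linked are unaffected. The point limits what may be said about impact and benefit, and it should be fixed.

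**What to change.** 1. In Data collection and analyses, state that no test or effect claim will be made against the 100%-positive baseline. Report the proportion still positive at 3 months on each screen and on both, with 95% confidence intervals and the number reached, as description.
2. In the Phase 2 section and in Limitations and challenges, replace the references to impact, the directional hypothesis and the benefits aim with a stated intention to describe change. Name selection on the outcome and regression to the mean as a limitation, and note that health, quality of life and utilization measured around an index ED visit may also regress.
3. If connected and non-connected patients are to be compared, state that contrast and label it exploratory and open to confounding.

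Using patients positive on only one screen as a utilization comparator is not advised. They differ in baseline vulnerability, may themselves be referred under the either-or-both wording, and say nothing about the re-screen.

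The cost is wording and a short table. The downside is a less favourable claim.
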